## Abstract

**Background::**

Anorexia is a common cause of malnutrition and is associated with negative effects on the quality of life (QOL) for patients with cancer. Management of appetite is the key to improving both the QOL and the prognosis for such patients. Yukgunja-tang (YGJT) is a traditional herbal medicine extensively prescribed in Korea as a remedy for various gastrointestinal syndromes. Currently, no standardized herbal medicine treatment exists for patients with cancer who are suffering from anorexia after surgery, chemotherapy, and/or radiotherapy. For that reason, this study aims to examine the efficacy and the safety of using YGJT to treat anorexia in such patients and to establish whether or not YGJT can be recommended as the primary therapy.

**Methods::**

We will enroll 52 cancer patients diagnosed with anorexia. The enrolled participants will be randomly allocated to 2 groups: The control group will receive nutrition counseling, and the YGJT group will receive nutrition counseling and be administered YGJT at a dose of 3 g twice a day for 4 weeks (a total of 56 doses of 3.0 g per dose). The primary outcome of this study is the change in the score on the anorexia/cachexia subscale (A/CS) of the Functional Assessment of Anorexia/Cachexia Therapy (FAACT). The secondary outcomes are the changes in the FAACT score with the A/CS score excluded, the score on the Visual Analogue Scale (VAS) for appetite, the weight and the body mass index (BMI), and laboratory tests for compounds such as leptin, tumor necrosis factor-α (TNF-α), ghrelin, and IL-6. All variables related to the safety assessment, such as vital signs, electrocardiography results, laboratory test results (CBC, chemistry, urine test), and adverse events, will be documented on the case report form (CRF) at every visit.

**Conclusion::**

This study is the first randomized controlled trial to investigate the efficacy and the safety of using YGJT for treating patients with cancer-related anorexia in Korea. We designed this study based on previous research about YGJT. This study will serve as a pilot and provide data for planning further clinical trials on herbal medicine and cancer-related anorexia.

**Trial registration::**

Clinical Research Information Service (CRIS), Republic of Korea, ID: KCT0002847. Registered retrospectively on 3 April 2018.

## Introduction

1

Anorexia is defined as an involuntary loss of appetite.^[1]^ It is a common cause of malnutrition and is associated with negative effects on the quality of life (QOL) in patients with cancer.^[2,3]^ Its symptoms involve decreased dietary intake and body weight loss if it gets worse. Studies have shown that 30% to 60% of patients with cancer-related anorexia are malnourished, which is usually associated with long hospitalization.^[4,5]^ Thus, one may conclude that cancer and its treatments may cause malnutrition and side effects that affect the nutritional status of patients suffering from the condition.^[3]^

Weight loss caused by malnutrition is associated with poor prognosis, such as short median survival, low chemotherapy response rate, and decreased performance status.^[6]^ Therefore, cancer-related anorexia, which is usually followed by loss of weight, is a distressing symptom for patients with cancer. This symptom may progress to precachexia, cachexia, and sarcopenia. Relieving anorexia has not only a supplementary, but also an essential therapeutic, aim of improving both the QOL and the prognosis for such patients.

Radical treatment to relieve cancer-related anorexia and cachexia syndrome (CACS) is assuredly required if patients are to be cured. However, if such an approach does not work, another option would be to increase nutritional intake through dietary counseling and education and through the administration of oral nutritional supplements. Appetite stimulants, such as corticosteroids (dexamethasone, methylprednisolone, and prednisolone) and progestins (medroxyprogesterone and megestrol acetate) are recommended for patients with anorexia.^[7]^ However, long-term and high-dose use of corticosteroids has been found to be associated with significant adverse events, including immunosuppression, hyperglycemia, muscle weakness/wasting, and fluid retention.^[8]^ Adverse events associated with the use of progestins include peripheral edema, hyperglycemia, hypertension, thrombotic events, breakthrough vaginal bleeding, Cushing syndrome, alopecia, and adrenal suppression, leading to adrenal insufficiency if abruptly stopped.^[9]^ The 2 above-mentioned categories of drugs, which are recommended as standard therapy for patients suffering from CACS, have been used for patients in whom short-term benefit is desired and for those with months-to-weeks life expectancy.^[8,10]^

Some patients seek to receive alternative safe and effective therapies such as herbal medicines for the treatment of cancer-related anorexia.^[11]^ Yukgunja-tang (YGJT), also known as Rikkunshito in Japan and Liu-Jun-Zi-Tang in China, is a traditional herbal medicine extensively prescribed in East Asian countries for the treatment of patients with various gastrointestinal syndromes, such as anorexia, nausea, dyspepsia, gastritis, and gastroesophageal reflux disease.^[12–18]^ A number of experimental studies have shown that YGJT may be effective in treating cisplatin-induced anorexia.^[19–21]^ However, additional clinical evidence for YGJT being a practical approach to treating such patients is needed. Therefore, we designed a randomized, controlled clinical trial to examine the efficacy and the safety of using YGJT to treat anorexia in patients suffering from cancer. Also, this pilot study will be performed to gather more evidence in support of recommending YGJT as a standard treatment for patients with cancer-related anorexia.

## Methods

2

### Study design

2.1

This study is a double-blind, randomized, controlled trial that aims to examine the efficacy and the safety of using YGJT to treat patients with cancer-related anorexia. All patients fulfilling the eligibility criteria will be selected. The enrolled participants will be randomly allocated to 2 groups: The control group will receive nutrition counseling, and the YGJT group will receive nutrition counseling and be administered YGJT. Figure 1 shows the schematic flow of this YGJT clinical trial.

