### Randomization and allocation

2.7

After informed consent has been obtained, random assignment will be performed by using a computer-generated, blocked, random-allocation sequence with an allocation ratio of 1:1. Each participant will be assigned to either the YGJT group or the control group according to a pregenerated randomization table and an assigned randomized number, which will be prepared in advance. Computer-generated block randomization, with block sizes of 4 and 8, will be done by a member of the Department of Information and Statistics, Chungnam National University, Daejeon, Korea; that member will have no clinical involvement in the trial. This procedure will ensure that the allocation is securely concealed from the researchers who will subsequently inform the patients of their allocations.

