### Interventions

2.8

The participants in the control group will be provided nutrition counseling on recommended chemotherapy, radiation, postoperative, and cancer-preventive diets. In addition to nutrition counseling, participants in the YGJT group will be administered YGJT at a dose of 3 g twice a day before meals for 4 weeks, for a total of 56 doses of 3.0 g per dose. Kolmarpharma Co, Ltd, produces the YGJT in accordance with Korea Good Manufacturing Practice (KGMP) standards. YGJT is manufactured by spray-drying a hot water extract of a mixture of 8 varieties of the following crude drugs: Atractylodis lanceae rhizoma (4.0 g), Ginseng radix (4.0 g), Pinelliae tuber (4.0 g), Poria cocos (4.0 g), Zizyphi fructus (2.0 g), Aurantii nobilis pericarpium (2.0 g), Glycyrrhizae radix (1.0 g), and Zingiberis rhizoma (0.5 g). These raw materials will be extracted and concentrated to 3 g per dose. The daily doses follow the recommended dosage method of the Korea Ministry of Food and Drug Safety (MFDS). During the trial, participants will be prohibited from receiving any other treatment for anorexia.

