#### Primary outcomes

2.9.1

The primary outcome is the change in the score on the anorexia/cachexia subscale (A/CS) of the Functional Assessment of Anorexia/Cachexia Therapy (FAACT) between baseline (visit 2) and the end of the administration period (visit 4). The FAACT is a clinical questionnaire for assessing the general aspects of QOL, as well as specific anorexia-related concerns, in patients with cancer. Especially, the A/CS has 12 items focusing on anorexia and cachexia among the total 39 items. The Korean version of FAACT, which was translated by the Functional Assessment of Chronic Illness Therapy (FACIT) organization, will be used. A trained investigator using standards operating procedures (SOPs) will determine and record the A/CS score at each visit.

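### Section 2.1 calls the trial double-blind, but the control group gets counselling only, without placebo, and patients are told their allocation, so the patients who supply the primary outcome are not blind

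*Protocol article*

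**What the plan says.** All references are to the protocol article.

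- Section 2.1 (Study design) gives the label: "This study is a double-blind, randomized, controlled trial that aims to examine the efficacy and the safety of using YGJT".
- The same section describes the arms: "The control group will receive nutrition counseling, and the YGJT group will receive nutrition counseling and be administered YGJT".
- Section 2.8 (Interventions) repeats this in more detail. For the control arm: "The participants in the control group will be provided nutrition counseling on recommended chemotherapy, radiation, postoperative, and cancer-preventive diets". For the experimental arm: "In addition to nutrition counseling, participants in the YGJT group will be administered YGJT at a dose of 3 g twice a day", continued for 4 weeks (56 doses). The abstract gives the same two arms. No placebo, sham or dummy preparation appears anywhere.
- Section 2.7 (Randomization and allocation) says the procedure ensures that "the allocation is securely concealed from the researchers who will subsequently inform the patients of their allocations".
- Section 2.9.1 (Primary outcomes) makes the change in the FAACT A/CS from visit 2 to visit 4 the primary outcome, and describes the instrument: "The FAACT is a clinical questionnaire for assessing the general aspects of QOL, as well as specific anorexia-related concerns, in patients with cancer". On collection it says: "A trained investigator using standards operating procedures (SOPs) will determine and record the A/CS score at each visit". It does not say whether this investigator knows the arm.
- The limitations in the Discussion cover the small sample, the difficulty of attributing anorexia to the cancer or its treatment, and the mix of cancer types and stages. Absence of blinding is not among them.

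**The concern.** A double-blind label tells the reader that patients, at least, did not know their arm. Under the arms described they must know it: one group takes a herbal preparation twice a day and the other takes nothing, and the protocol adds that patients are told.

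This matters because the primary outcome and the appetite VAS depend on what patients say about their own appetite and concerns. Patients who know they receive an active product, or know they do not, may answer differently for that reason alone. The group difference then estimates the effect of YGJT together with any effect of expecting benefit.

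Section 2.6 says the results are meant to inform the design of a confirmatory trial, and the Introduction says they are meant to support recommending YGJT as a standard treatment. An effect size taken from an open comparison but reported as double-blind could be used in both places without the necessary caution.

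**Working it through.** **1. The label against the design.** No arithmetic is needed.

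| Question | What the article states | Consequence |
|---|---|---|
| Is there a placebo? | None in the abstract, 2.1 or 2.8 | Patients can tell their arm from whether they take the product |
| Are patients told? | Yes, by researchers (2.7) | Patients are unblinded, and so are those researchers |
| Who supplies the primary data? | Patients, through a questionnaire (2.9.1) | The outcome is open to expectation |
| Is the person recording the A/CS blind? | Not stated (2.9.1) | Cannot be decided from the article |

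The first two rows settle the point. Figure 1 and Table 1 are not shown, but the intervention text is complete without them.

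**2. The plan's own sample size.** Section 2.6 uses a standardised effect of 0.9, two-sided 5%, 80% power and v = 40:

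n = 2 × (1/0.9²) × (2.0211 + 0.8507)² = 2 × 1.2346 × 2.8718² = 20.36, rounded up to 21 per arm; 21 × 1.2 = 25.2, rounded up to 26 per arm, 52 in total.

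The stated 52 reproduces, and the blinding point does not touch it. It supplies the 21 per arm used next.

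**3. Illustration of what unblinded reporting could do.** The bias sizes are assumptions; the article gives no figure. Let YGJT have no true effect, and let reporting shift the mean A/CS difference by b standard deviations in favour of YGJT. For a two-sample t test with n per arm, the statistic is noncentral t with 2n − 2 degrees of freedom and noncentrality b × √(n/2). With n = 21 there are 40 degrees of freedom, the critical value is 2.0211 and √(21/2) = 3.240.

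| Assumed b (SD) | Noncentrality, n = 21 | P(p < 0.05), n = 21 | of which favouring YGJT | P(p < 0.05), n = 26 |
|---|---|---|---|---|
| 0 | 0 | 5% | 2.5% | 5% |
| 0.2 | 0.648 | 9.7% | 9.2% | 10.9% |
| 0.3 | 0.972 | 15.8% | 15.6% | 18.6% |
| 0.4 | 1.296 | 24.4% | 24.4% | 29.3% |

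**4. Carry-over to planning.** The same b is added on average to the effect size taken forward. Set against the planning value of 0.9, biases of 0.2 to 0.4 SD are 0.2/0.9 = 22% to 0.4/0.9 = 44% of it.

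**The case against.** The strongest reply is that an article condenses the full protocol. Version 2.2 exists and is not shown, and who among assessors and analysts is blinded is the kind of detail left to it. That stands for the assessor. It does not rescue the label, because no unseen procedure can blind patients who have been told their arm.

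A second reply is that the label occurs only once. The abstract and Introduction say only randomised and controlled, and the arms are described openly. That is fair: it is speculation to say that readers will credit the whole difference to YGJT. But a false statement in the design section still needs correcting.

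Three stronger readings are tempting and are not supported:

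- **That the scoring investigator knows the arm and adds rater bias.** Section 2.9.1 does not say so, and does not identify this person with the researchers who inform patients. Section 2.11 leaves data collection and analysis to the study investigators, which makes this a possible risk but does not establish it. A blinded assessor would in any case make the trial assessor-blind at most, since unblinded patients would still give the answers.
- **That the investigator, and not the patient, rates the A/CS.** The wording also fits an investigator totalling a form that the patient has completed.
- **That the trial has no protection from bias.** Random allocation, blocks of 4 and 8, a sequence generated by someone without clinical involvement, and concealment before assignment are all unaffected. Concealment is a separate safeguard from blinding.

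The numerical illustration is also open to the objection that its bias sizes have no source in the article. That is correct, and the contradiction does not depend on them.

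**Conclusion.** The label is wrong as written. Participants, and the researchers who inform them, are not blind, and the article claims a property that its own design sections exclude. The consequence is confined to interpretation: differences in the A/CS and the appetite VAS may include expectation effects, and the Discussion gives no warning of this. Assessor blinding is undescribed, not shown to be absent.

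No size can be derived from the article. Under an assumed bias of 0.2 to 0.4 SD, no true effect, 21 evaluable patients per arm and a two-sample t test, the chance of a significant result in either direction is about 10% to 24% instead of 5%.

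An open add-on comparison is a legitimate choice for an exploratory pilot. The fault lies in the label and the missing caveat, and the point does not call for a placebo arm.

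**What to change.** 1. In 2.1 and in all reports, replace double-blind with open-label, randomised, nutrition-counselling-controlled. Use assessor-blind, participants unblinded only if a blinded assessor is actually in place, and then say who it is.
2. State that the effect estimated is that of open-label YGJT plus counselling against counselling alone, and that it may include expectation effects.
3. Add this to the limitations in the Discussion, and attach it to any use of the observed effect size in planning the confirmatory trial.
4. Clarify in 2.9.1 that patients answer the A/CS items and the investigator only records and totals them. Keep the mode of administration the same at visits 2 and 4. Registration was retrospective (3 April 2018), so enrolment may already have begun, and a change between the two visits could make a patient's scores non-comparable. If practice so far has differed from this, it should be reported as it was.

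The cost is a change of wording and a less favourable design label. No new arm, staff or procedure is needed, provided the mode of collection is not altered part-way.

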**Figure 1 F1:**
[figure not shown]
Study flow chart of the YGJT clinical trial.

### Recruitment

2.2

Participants will be recruited through advertisement on bulletin boards at and the homepage of Dunsan Korean Medicine Hospital of Daejeon University in Daejeon, Republic of Korea. Detailed information on the trial, including study period, purpose of study, inclusion and exclusion criteria, and intervention, will be posted on a recruitment notice, and those patients who sign the informed consent forms will voluntarily visit the trial site.

### Inclusion criteria

2.3

Participants meeting the following criteria will be included: Patients who have a histologically or cytologically confirmed solid tumor; individuals who are suffering from anorexia; men and women aged 20 to 80 years who can write, read, and understand; score on the Visual Analog Scale (VAS) for anorexia ≥ 40/100 mm; neutrophils ≥ 1500/μL, platelets ≥ 100,000/μL; total bilirubin of the maximum normal level or less (1.2 mg/dL); alanine aminotransferase (ALT) and aspartate aminotransferase (AST) levels lower than twice the upper limit for normal (35/45U/ℓ); creatinine level lower than 1.5 times the upper limit for normal (1.09 mg/dL); patients who provide written informed consent for participation in the trial.

### Exclusion criteria

2.4

Participants meeting one or more of the following criteria will be excluded: Patients unable to intake medicine orally; patients who are undergoing chemotherapy and those who completed such therapy less than 1 month earlier; patients who have survived at least 5 years after having been diagnosed with cancer; Eastern Cooperative Oncology Group (ECOG) performance status score ≥ 3; patients who have dementia, delirium or depression; patients who score more than 7 points on the Numeric Pain Rating Scale within 2 weeks of screening; patients who have diseases like hypoadrenalism that can influence appetite; patients who are taking appetite stimulants such as megestrol acetate, corticosteroids, and thalidomide; patients who are judged to be inappropriate for inclusion in this study; women who are pregnant or are planning to become pregnant.

### Withdrawal criteria

2.5

Participants who meet the withdrawal criteria will be dropped from the trial. Participants who withdraw or are dropped after randomization will be followed for outcomes. The withdrawal criteria include the use of any forbidden medication or treatment during the trial that could affect the study result, the participant's withdrawal of consent, the occurrence of a serious adverse event, the detection of eligibility violations, the occurrence of other significant protocol violations during the trial, and the investigator's decision to terminate the process for the sake of the participant's health.

### Sample size

2.6

This study is an exploratory trial conducted before a confirmatory trial to establish the validity of using YGJT to treat patients with cancer who are suffering from anorexia. The efficacy of YGJT will be examined in order to provide information that will lead to a better design for a future clinical trial. Considering a dropout rate of 20%, we calculated that a total of 52 subjects, 26 per group, should be enrolled in this study. The sample size was set using an effective size of 0.9, which is the ratio of the standard deviation of each group from the mean difference of outcomes between the YGJT group and the control group at a significance level of 5% and a power of 80%. The formula for estimating the sample size is as follows:  

where n is the approximate sample sizes required per group, *t*_*α,v*_ is the 97.5 percentile score of the *t* distribution with *v* degrees of freedom, and *t*_*β*(1),*v*_ is the 80 percentile score of the *t* distribution with *v* degrees of freedom. If *v* = 40, n′ ≥ 2 × 1.2346 × (2.0211 + 0.8507)^2^ = 20.3632 (21). For a dropout rate of 20%, the sample size for each group is given by n = 21 × 1.2 = 25.2 (26). Therefore, a total of 52 subjects, 26 in each of the 2 groups, will be enrolled in this study.

### Randomization and allocation

2.7

After informed consent has been obtained, random assignment will be performed by using a computer-generated, blocked, random-allocation sequence with an allocation ratio of 1:1. Each participant will be assigned to either the YGJT group or the control group according to a pregenerated randomization table and an assigned randomized number, which will be prepared in advance. Computer-generated block randomization, with block sizes of 4 and 8, will be done by a member of the Department of Information and Statistics, Chungnam National University, Daejeon, Korea; that member will have no clinical involvement in the trial. This procedure will ensure that the allocation is securely concealed from the researchers who will subsequently inform the patients of their allocations.

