#### Subgroup analysis

2.9.4

Participants will be subdivided into the following 3 subgroups: patients who complain of anorexia after surgery, patients who complain of anorexia during radiation therapy or recent radiation therapy, patients who complain of anorexia more than 1 month after chemotherapy. Comparisons of the YGJT group and the control group will also be performed at the subgroup level.

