#### Subgroup analysis

2.10.3

The efficacy of YGJT between subgroups will be evaluated as follows: comparison of the YGJT efficacy for each of the subgroups in the YGJT group with that of the corresponding subgroup in the control group and comparison of the YGJT efficacy among the 3 subgroups of the YGJT group. The statistical significance of any differences between the YGJT group and the control group, among the 3 subgroups, will be analyzed using a generalized linear model with either the Wilcoxson rank sum test or the Kkruskal–Wallis test. All tests will be 2-sided tests, and the significance level will be 0.05.

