Even though this trial may provide scientific evidence for the efficacy of YGJT in relieving anorexia, this study has limitations that are mostly derived from its relatively small sample sizes. In addition, identifying clearly whether anorexia resulted from cancer or from cancer treatment, such as surgery, chemotherapy, or radiotherapy, is problematic. Therefore, the particular mechanisms underlying anorexia suffered by cancer patients cannot be clearly determined. Considering recruitment feasibility, patients with various cancer types and with different stages of cancer will be recruited in this pilot study. Further studies are needed to estimate the influences of both the specific types and stages of cancer and the surgical status. Despite these limitations, this study should serve as a pilot report to plan further clinical trials on herbal medicine and cancer-related anorexia.

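### Treatment setting defines the planned subgroup comparisons but enters neither the randomisation nor the pooled primary comparison, which costs precision if the settings differ

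*Protocol article*

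**What the plan says.** All references are to the protocol article.

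- **2.7 Randomization and allocation** describes 1:1 allocation from a single table prepared in advance: "Computer-generated block randomization, with block sizes of 4 and 8". It gives the ratio, the block sizes and who generates the sequence. It names no stratification factor.
- **2.9.4 Subgroup analysis** divides participants by the setting of their anorexia (after surgery; during or soon after radiotherapy; more than 1 month after chemotherapy) and adds: "Comparisons of the YGJT group and the control group will also be performed at the subgroup level".
- **2.10.3 Subgroup analysis** repeats that commitment, adds a comparison among the three settings within the YGJT arm, and sets the error level: "All tests will be 2-sided tests, and the significance level will be 0.05".
- **2.10.1 Efficacy assessment** covers the pooled change from visit 2 to visit 4 with simple tests. It names no adjustment for setting. (Whether the paired tests named there suit a between-group comparison is a separate matter.)
- **2.6 Sample size** calls the trial exploratory and plans that "a total of 52 subjects, 26 in each of the 2 groups, will be enrolled in this study".

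**The concern.** Setting is the only patient characteristic on which the protocol builds a subgroup analysis, yet the design does not control it. Blocking equalises the total arm sizes. It does nothing for the mix of settings within each arm, so in a trial of 52 the mix is left to chance.

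If the 4-week change in A/CS differs by setting, two things follow. Differences between settings add to the residual variance of an unadjusted comparison, and in any one trial an uneven mix moves the estimate. Both make the treatment estimate less precise than the same patients could deliver. That matters because the trial exists to inform the design of a later one. The split of patients between arms within each planned subgroup comparison is also uncontrolled.

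**Working it through.** **Inputs from the protocol article.** Effect size 0.9, 80% power, two-sided 5%, 20% dropout, 26 per arm (2.6); 1:1 blocks of 4 and 8 (2.7); three settings (2.9.4).

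**Assumed, because the document gives no figures.** The mix of settings (equal thirds unless stated) and the spread of mean A/CS change across settings (1 or 2 within-setting SD from lowest to highest).

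**1. The plan's own figure.** 2 × (1/0.9²) × (2.0211 + 0.8507)² = 2 × 1.2346 × 8.247 = 20.36, so 21 per arm; 21 × 1.2 = 25.2, so 26. The stated 52 reproduces. After 20% dropout, 26 × 0.8 = 20.8, about 21 per arm. An exact two-sample t test with 21 per arm has 81% power for 0.9 SD.

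**2. Chance imbalance in the mix.** Simulation with 26 per arm and equal thirds:

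- some setting differs between arms by 5 or more patients: about 38%; by 6 or more: about 24%;
- with blocks of 4 and 8 simulated explicitly, some setting's share differs by 20 percentage points or more in 25% of trials at N = 52 (13% with a 70/20/10 mix) and in 33% at N = 42 (20% with 70/20/10);
- with a separate blocked list per setting, the 5-patient and 20-point imbalances both fall to about 0%.

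**3. Size of the shift in one trial.** A 20-point shift between two settings whose mean change differs by 0.5 to 1.0 SD moves the estimate by 0.20 × 0.5 = 0.1 SD to 0.20 × 1.0 = 0.2 SD, against a planned 0.9 SD.

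**4. Type I error.** The simulated unadjusted two-sample test at N = 42, unstratified, rejects a true null in 5.1% (spread 1 SD) and 5.6% (spread 2 SD) of trials. That is nominal within simulation error.

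**5. Power.** Take within-setting SD 1 and setting means −d/2, 0 and +d/2 in equal thirds. The between-setting variance is then d²/6.

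- d = 1: total SD = √(1 + 0.167) = 1.080; standardised effect 0.9/1.080 = 0.833; power with 21 per arm about 74–75%.
- d = 2: total SD = √(1 + 0.667) = 1.291; standardised effect 0.9/1.291 = 0.697; power about 59–60%.

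| Analysis, 21 per arm | Settings do not differ | Spread 1 SD | Spread 2 SD |
|---|---|---|---|
| Unstratified, unadjusted | 81% | 74% | 59–61% |
| Unstratified, adjusted | 79% | 78–79% | 79–80% |
| Stratified, unadjusted | not simulated | 76% | 62% |
| Stratified, adjusted | not simulated | 81% | 81% |

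Ranges reflect separate simulation runs. Adjustment does most of the work. Stratifying and then ignoring the strata gains little and makes the test conservative (simulated type I error 3.3% and 1.7%).

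**6. Which SD the 0.9 refers to.** Section 2.6 says "The sample size was set using an effective size of 0.9" and relates it to the SD of each group, which may already contain the spread between settings. If so, unadjusted power stays at 81% and the within-setting effect is larger: 0.9 × 1.080 = 0.972 or 0.9 × 1.291 = 1.162. The simulated standard error of the adjusted estimate is about 0.319 or 0.316. The ratio to the standard error, less the critical t value of about 2.02, is 0.972/0.319 − 2.02 = 1.03, or about 85% power, and 1.162/0.316 − 2.02 = 1.66, or about 95%. The precision gain from adjusting is the same; it then comes on top of the planned power.

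**7. Subgroup cells (N = 52).**

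| Event | Mix | Unstratified | Stratified |
|---|---|---|---|
| Some cell of 2 or fewer | equal | 1.6% | 0.1% |
| Some cell of 2 or fewer | 60/30/10 | 76% | 65% |
| Some cell of 5 or fewer | equal | 46% | about 15% |
| Some cell of 5 or fewer | 50/25/25 | 84% | about 62% |

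With perfect balance and equal thirds there are 26/3 ≈ 8.7 per arm per setting, and power for 0.9 SD is about 43% with 9 per arm and 34% with 7.

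**The case against.** The strongest case against is that unstratified blocked randomisation is an accepted choice for a 52-patient exploratory trial, and that nothing in the text is an error or a contradiction. That stands: this is an inexpensive improvement, not a correction of a mistake.

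Three stronger readings are tempting, and the document does not support them.

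- **That imbalance could pass for a drug effect.** Randomisation keeps the test valid, type I error stays near 5%, and the plausible shift in one trial (0.1–0.2 SD) is small beside 0.9 SD.
- **That missing stratification would leave subgroup arms nearly empty.** With an equal mix, cells of 2 or fewer are rare. With an uneven mix they are common even when stratified. The cause is mainly the sample size and the mix.
- **That the protocol itself expects the settings to run different courses.** It only subdivides and compares. The Discussion's admission of heterogeneity, "Considering recruitment feasibility, patients with various cancer types and with different stages of cancer will be recruited in this pilot study", concerns tumour type and stage, not setting.

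It may also be said that covariate adjustment belongs in an analysis plan that is not shown, and that 2.10.3 mentions a generalized linear model. Both are fair in part. But that model is described for the subgroup question, while 2.10.1 names its tests without it. Stratification has to be settled before allocation starts, and 2.7 is specific about everything else in the scheme.

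Finally, the categories can overlap, and the Discussion concedes that it is hard to attribute anorexia to one treatment. This is a real cost of the fix. The planned subgroup analysis carries the same cost, since it too must place each patient in a category.

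**Conclusion.** The point holds as a question of efficiency. As described, setting is controlled neither in allocation nor in the primary comparison, although the protocol intends to test within it. A between-arm difference of 5 or more patients in some setting has a probability of about 38% under an equal mix.

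The consequence is lost precision and not bias over repeated randomisation. With 21 per arm and 0.9 within-setting SD, power is about 74% or 59% unadjusted against about 79% adjusted, for settings spanning 1 or 2 SD. If the settings do not differ, nothing is lost by the present plan. A reader might infer that the trial therefore misses its stated 80%. That does not follow, because the planned SD may already include the spread between settings.

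The figures rest on assumed mixes and an assumed spread, for which the document gives no data. The subgroup comparisons remain weak whatever is done about allocation.

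**What to change.** 1. Record one setting for each patient at screening, before allocation. Write a rule for patients who fit more than one category (for example surgery followed by chemotherapy) and for those who fit none, since the printed inclusion criteria require none of the three treatments.
2. Include that pre-allocation setting as a factor in the primary between-group model of A/CS change.
3. If enrolment has not begun, have the independent statistician prepare a separate 1:1 list with small blocks for each setting. If enrolment has begun, keep the existing list and rely on step 2, which recovers most of the precision.
4. Describe the within-setting results as descriptive estimates with confidence intervals.

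**Cost.** Two extra lists and one data field, with no added patients or visits. About 2 points of power are lost if setting is not prognostic (81% to 79% with 21 per arm). Incomplete final blocks can leave the arms slightly unequal: with blocks of 4, by at most 2 per list, so at most 3 × 2 = 6 overall. Subgroup arms will still be small.
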